#### Female-specific variables

The date of the last menstruation will be recorded, because it may impact the study variables.

#### Anthropometric variables

The height will be measured, with the subject standing barefoot, to record the average of two readings rounded to the nearest centimetre using a portable system (Seca 222; Medical scale and measurement system, Birmingham, UK).

The body weight will be measured, with the subject barefoot and wearing light clothing, to record the average of two readings rounded to 100 g using a standard electronic balance (Seca 770; Medical scale and measurement system, Birmingham, UK) that is properly calibrated (precision ± 0.1 kg).

Following the recommendations of the Spanish Society for the Study of Obesity (SEEDO) [36], the waist circumference will be measured in duplicate at the level of the midpoint between the last rib and the iliac crest (with the subject standing without clothing) using a flexible tape parallel to the floor after inspiration. Hip circumference will be similarly measured at the level of the trochanters.

#### Peripheral blood pressure

Three measurements of systolic (SBP) and diastolic (DBP) blood pressure will be performed using the average of the last two with a validated Omron M10-IT model sphygmomanometer (Omron Healthcare, Kyoto, Japan). The measurements will be made on the participant’s dominant arm in a seated position after at least 5 minutes of rest with a cuff of appropriate size as determined by measurement of the upper arm circumference and following the recommendations of the European Society of Hypertension [37].

#### Arterial stiffness and central haemodynamic parameters

The Mobil-O-Graph® device [38] will be used to estimate cardiac output and total peripheral vascular resistance and to measure central blood pressure (CBP), pulse wave velocity (PWV), reflection coefficient and augmentation index (AIx). This is affected by heart rate (HR), so its values will be corrected to an HR of 75 bpm. This device will be scheduled to perform continuous measurements at –10, 0, 15, 30, 45, 60, 75, 90, 105 and 120 minutes with the subject sitting and resting his arm on a rigid surface.

#### Laboratory variables

At the time of study entry and prior to the first intervention visit, fasting plasma creatinine, serum total cholesterol, high-density lipoprotein (HDL) cholesterol, low-density lipoprotein (LDL) cholesterol and triglyceride values will be determined using standard enzymatic automated methods.

During each study visit, three cannula blood samples will be collected at –10, 60 and 120 minutes to measure serum glucose and insulin levels by ultraviolet-visible spectrophotometry and chemiluminescence, respectively. Serum will be isolated by centrifugation and stored in a –20 °C freezer within 48–72 hours until analysis. Samples will be treated and centrifuged by a single researcher under standardised conditions. The analysis will be performed in a laboratory in external quality assurance programs of the Spanish Society of Clinical Chemistry and Molecular Pathology.

#### Cognitive performance evaluation variables

For each of the three visits and for each evaluation within the same visit, a list of 15 different words from the Rey Auditory Verbal Learning Test and its alternative versions [39–41] will be used to evaluate the immediate verbal memory via immediate recall over three attempts. Delayed verbal memory will be assessed by free recall of the words learnt in the first part of the evaluation after a period of 10 minutes. Phonological fluency will be explored by enumerating for one minute as many words as possible starting with different letters [42]. The Trail Making Test A will be used to assess attention and processing speed, while executive functions will be explored using the Trail Making Test B [43]. Working memory will be traced with the WAIS Digit Span Backward test [44]. Finally, sustained and selective attention, executive functions and processing speed will be explored with the Stroop test [45].

### Statistical analysis

The normal distribution of variables will be verified using a Kolmogorov-Smirnov test. Quantitative variables will be displayed as the mean ± standard deviation if normally distributed or as the median (interquartile range) if asymmetrically distributed. The data will be quantitated using the repeated measures for analysis of variance (ANOVA) or the Friedman test if the data are non-normally distributed. To compare the differences among the three types of breakfast, the ANOVA test will be used, or the Wilcoxon test if the data are non-normally distributed. We will use the least significant difference (LSD) test as post hoc analysis. The relationship of quantitative variables to each other will be tested using Pearson’s or Spearman’s correlation as appropriate. The effect of the interventions can be modified by conditions such as the last menstruation date. To control the effect of confounders on the study results and to adequately evaluate the effect of the interventions, a multivariate analysis will be performed using the general linear model (GLM) in basic or extended models. The contrasting hypothesis will establish an alpha risk of 0.05 as the limit of statistical significance. The data will be analysed using IBM’s SPSS Statistics for Windows version 23.0 (IBM Corporation, Armonk, NY, USA).

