## Methods/design

### Design and setting

We designed a controlled crossover clinical trial where each subject will complete three interventions (control condition, high GI breakfast and low GI breakfast) with a washout period of one week between each trial. The order will be determined by a randomisation sequence generated using randomization.com software (http://www.randomization.com) (Fig. 1). The SPIRIT checklist is provided as Additional file 1.

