### Sample size

The primary outcome variable is change in central augmentation index (AIx). The Conduit Artery Function Evaluation (CAFE) study [8] found a reduction in cardiovascular events associated with a decline of 6.5 (5.8, 7.3) points in the AIx. This is the basis of our calculation. The power calculation was a repeated measures design and compared both intervention breakfasts with a control condition with an alpha risk of 0.05 and a beta risk of 0.2. The standard deviation (SD) was 10 with a correlation coefficient between the initial and final measurement of 0.7. Thus, 40 subjects are required to detect a minimum difference of 5 points in the AIx between two intervention breakfasts. A loss to follow-up of 5 % was estimated.

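### The repeated-measures ANOVA named for this three-visit crossover analyses complete cases only, so one missed visit, or one missing reading the model needs, removes a participant from the three-breakfast comparison

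*Protocol article*

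**What the plan says.** - Design and setting: "each subject will complete three interventions (control condition, high GI breakfast and low GI breakfast) with a washout period of one week".
- Arterial stiffness and central haemodynamic parameters: "This device will be scheduled to perform continuous measurements at –10, 0, 15, 30, 45, 60, 75, 90, 105 and 120 minutes". That is 10 augmentation index (AIx) readings per visit and 3 × 10 = 30 per participant.
- Sample size: the primary outcome is change in central AIx, with no time point or summary of the post-meal curve named in that section. The inputs are "with an alpha risk of 0.05 and a beta risk of 0.2" and "The standard deviation (SD) was 10 with a correlation coefficient between the initial and final measurement of 0.7". The result is that "40 subjects are required to detect a minimum difference of 5 points in the AIx between two intervention breakfasts", followed by "A loss to follow-up of 5 % was estimated".
- Statistical analysis: "The data will be quantitated using the repeated measures for analysis of variance (ANOVA) or the Friedman test if the data are non-normally distributed". A further sentence compares the three breakfasts by ANOVA, or by Wilcoxon if non-normal, with least significant difference (LSD) post hoc tests. A general linear model is named for confounders. The software is SPSS 23.

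The article names no mixed model, no imputation and no rule for participants with incomplete data.

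**The concern.** Classical repeated-measures ANOVA, as run in the SPSS general linear model procedure, needs a full row per participant. In a three-condition crossover, someone who attends both breakfasts but misses the water visit is dropped. That participant's completed high- and low-GI visits then contribute neither to the overall test nor to LSD contrasts taken from it. The same happens if one reading that the model needs is missing.

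Two things are at stake. One is precision: completed visits are thrown away in a small trial whose sample size has almost no slack. The other is the analysed set, which becomes those with complete attendance and complete readings. That is safe only if incompleteness is unrelated to outcome.

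The method is written into the text, so this concerns a stated choice and is not a detail left to a plan that is not shown.

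**Working it through.** **Step 1. Reproduce the 40.** Inputs from Sample size: difference 5, SD 10, correlation 0.7, alpha 0.05 (sidedness not stated; two-sided assumed), power 80 %.

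- SD of change = 10 × √(2 × (1 − 0.7)) = 7.746, variance 60.
- Difference of two changes uncorrelated across visits: variance 2 × 60 = 120, SD 10.95.
- n = (1.960 + 0.842)² × 120 / 5² = 7.849 × 4.8 = 37.7, so 38.
- 38 / 0.95 = 40.

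The stated figure is reproduced. It already contains the 5 %, so 40 − 38 = 2 incomplete participants are covered.

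**Step 2. When is the 5 % exceeded?** With independent failures at rate q over m required items, the complete share is (1 − q)^m. Setting this to 0.95 gives q = 1 − 0.95^(1/m).

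| Items that must be present | m | Break-even q |
|---|---|---|
| Three visits | 3 | 1.7 % |
| One baseline and one post-meal reading per visit | 6 | 0.85 % |
| All readings in one breakfast-by-time model | 30 | 0.17 % |

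**Step 3. Missed visits, 40 enrolled.** The documents give no rate, so a range is assumed. Power = Φ(5 / √(120/n) − 1.96). The complete-case n is 40(1 − q)³. The number with both the high- and low-GI visits is 40(1 − q)².

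| Missed per visit | Complete-case n | Power | High-low pairs kept | Power |
|---|---|---|---|---|
| 2 % | 37.6 | 80.0 % | 38.4 | 80.8 % |
| 3 % | 36.5 | 78.8 % | 37.6 | 80.0 % |
| 5 % | 34.3 | 76.2 % | 36.1 | 78.3 % |
| 10 % | 29.2 | 69.3 % | 32.4 | 73.8 % |

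**Step 4. Isolated failed readings, all visits attended (assumed rates).**

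| Failure rate | 6 needed: n left, power | 30 needed: n left, power |
|---|---|---|
| 0.5 % | 38.8, 81.2 % | 34.4, 76.4 % |
| 1 % | 37.7, 80.0 % | 29.6, 69.9 % |
| 2 % | 35.4, 77.5 % | 21.8, 56.8 % |

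At 1 % failures an all-available analysis still uses 99 % of readings. The complete-case analysis keeps 94 % or 74 % of participants, depending on the layout.

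**Step 5. What the replacement model must contain.** Assume, for illustration only, SDs of 3.5 between visits within a person and 4.2 between readings, with n = 38. Take a high-low contrast on the mean of the 8 post-meal readings.

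- True variance per person = 2 × (3.5² + 4.2²/8) = 2 × (12.25 + 2.205) = 28.91, so SE = √(28.91/38) = 0.87.
- With a participant random effect alone, visit variation falls into the residual, which is about 17.64 + 10 × 12.25 × 2/29 = 26.1. The reported SE is about √(2 × 26.1/(8 × 38)) = 0.41.

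The reported SE is about half the true one. A nominal 1.96 then corresponds to about 0.93 true SEs, a false-positive rate of roughly one third. A visit-level term is therefore essential.

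**The case against.** A reader might go further in four ways that the article does not support.

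- **One failed reading in 30 excludes a participant.** Nothing says that all 30 readings enter one model. The outcome is a change, which might use one baseline and one post-meal reading per visit. The repeated-measures sentence can also be read as the time course within a visit, with the breakfasts compared under a separate sentence. The 30-reading case is therefore only one of several readings.
- **Friedman behaves in the same way.** It does drop incomplete blocks, but it is a one-way test. It needs 3 values across breakfasts or 10 across times, never 30. The Wilcoxon fallback is pairwise and would keep a completed high-low pair, so the problem lies in the parametric route.
- **The 5 % is too low.** No missed-visit or failed-reading rate is documented. The 5 % is described as loss to follow-up, and three short visits a week apart could stay within it. Only the break-even points can be stated.
- **Participants will skip the water visit selectively.** Participants are unblinded and could work out the remaining condition, but order is randomised and nothing in the article indicates differential attendance. This is conjecture.

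The power figures also depend on the planning variance. If the within-subject difference between breakfasts had SD 7.75 instead of 10.95, 19 complete participants would give 80 % power and about 30 would still give about 94 %.

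These objections limit the size of the problem. What stands is that a repeated-measures ANOVA across three breakfasts discards the completed visits of anyone who misses one, and the article names no alternative.

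**Conclusion.** The point holds as a weakness of the chosen method, with a conditional cost. The sample size covers two incomplete participants, and whether more will occur cannot be known from the article.

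For missed visits alone the gain from keeping completed visits is modest: about 2 percentage points of power at 5 % missed and between 4 and 5 at 10 %. For failed readings it depends on how many readings the model needs. It is small with two per visit and a low failure rate, and substantial if all 30 enter one model.

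These figures assume independent failures, a two-sided 0.05 test, the normal approximation, and the planning SD of 10.95 for a difference between two changes. The change is worth making because it is cheap and rests on a weaker missing-data assumption than complete-case analysis.

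**What to change.** In the Statistical analysis section, analyse AIx and the other repeated outcomes with a linear mixed model (MIXED in SPSS 23) on all available visits and readings:

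- fixed effects for breakfast, time, breakfast × time and period;
- a random participant effect and a random visit-within-participant effect, or an equivalent within-visit covariance. A participant effect alone is not adequate (Step 5 of the working).

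State that participants who miss a visit keep their completed visits in the analysis, and tabulate missed visits by the condition missed.

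The cost is revised wording and a different procedure in the software already named, with no extra participants or visits. The small downside is that the model relies on a missing-at-random assumption and on a covariance structure that has to be chosen.

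### The main comparison among the three breakfasts is assigned to a test not stated to be within-subject, with a two-condition rank test as its alternative, although every participant receives all three

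*Protocol article*

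**What the plan says.** The protocol's Design and setting section fixes a crossover: "We designed a controlled crossover clinical trial where each subject will complete three interventions", with a one-week washout and a randomised order. The Sample size section names the outcome: "The primary outcome variable is change in central augmentation index (AIx".

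The Statistical analysis section then takes four steps.
- It opens with a normality check: "The normal distribution of variables will be verified using a Kolmogorov-Smirnov test".
- It names repeated measures ANOVA, or Friedman for non-normal data. It does not say whether the repeated factor is time within a visit, breakfast, or both.
- A separate sentence covers the breakfast comparison: "To compare the differences among the three types of breakfast, the ANOVA test will be used, or the Wilcoxon test", with Wilcoxon reserved for non-normal data.
- It adds least significant difference (LSD) post hoc tests and a general linear model for confounders.

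For the breakfast comparison, no sentence names participant, period or sequence as a model term.

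**The concern.** The comparison among breakfasts is the trial's main question, and each participant contributes to all three arms of it. An ordinary ANOVA treats the arms as independent groups, so variation between people stays in the error term. The reason for choosing a crossover is to remove that variation.

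The alternative branch has its own fault. Wilcoxon, whether signed-rank or rank-sum, handles two conditions, so it cannot be the overall test among three. Friedman can, but the protocol names it in the neighbouring sentence.

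Two analysts following this section could therefore report different intervals and p-values for the primary outcome, and a preliminary normality test would decide which branch they took.

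**Working it through.** **Inputs from the protocol (Sample size).** SD 10 and correlation 0.7: "The standard deviation (SD) was 10 with a correlation coefficient between the initial and final measurement of 0.7". Error rates: "an alpha risk of 0.05 and a beta risk of 0.2" (two-sided assumed). Target: "40 subjects are required to detect a minimum difference of 5 points in the AIx between two intervention breakfasts". Loss to follow-up is 5%.

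**Assumed.** The correlation r between a person's AIx changes under two breakfasts is not given, so it is varied over 0, 0.3, 0.5 and 0.7. The stated 0.7 links initial and final measurements and says nothing about r.

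**Step 1: the plan's own figure.** SD of change = 10 × √(2 × (1 − 0.7)) = 7.75. For two independent groups, n = 2 × (1.960 + 0.842)² × 7.75² / 5² = 37.7, so 38 per group. Allowing for loss, 38 / 0.95 = 40. The stated 40 is reproduced exactly, with no credit taken for pairing between breakfasts. If 7.75 were instead the SD of a paired difference, n would be 18.8, so 19.

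**Step 2: standard error of a breakfast difference, 38 completers.**
- Unpaired: 7.75 × √(2/38) = 1.78.
- Within-subject: 7.75 × √(2 × (1 − r)/38).
- Ratio of the two: 1/√(1 − r).

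| r (assumed) | Within-subject SE | Unpaired SE / within-subject SE | Within-subject power for 5 points |
|---|---|---|---|
| 0 | 1.78 | 1.00 | about 79% |
| 0.3 | 1.49 | 1.20 | about 91% |
| 0.5 | 1.26 | 1.41 | about 98% |
| 0.7 | 0.97 | 1.83 | over 99% |

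Power uses the noncentral t distribution with 74 degrees of freedom (2 × 37). The unpaired calculation gives about 80% (111 degrees of freedom, 3 × 37).

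**Step 3: how the literal test behaves on crossover data.** The 80% is the planning figure for independent groups. To see what an ordinary ANOVA does when the data are in fact correlated, three conditions were simulated for 38 people, with equal correlations and 200,000 trials per setting. Assumed means were all equal for the type I error, and 0, 5 and 2.5 for power.

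| r | Overall type I error: plain / repeated measures | Overall power: plain / repeated measures | Pairwise LSD power for 5 points: plain / repeated measures |
|---|---|---|---|
| 0 | 0.050 / 0.050 | 70% / 70% | 80% / 79% |
| 0.3 | 0.015 / 0.050 | 71% / 85% | 84% / 91% |
| 0.5 | 0.003 / 0.051 | 72% / 95% | 88% / 98% |
| 0.7 | 0.0002 / 0.051 | 75% / over 99% | 93% / over 99% |

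The plain test falls well below its nominal 5% once r is positive. The pairwise loss is moderate. The loss in the overall test is larger, and it carries over to the pairwise results if LSD is used only after a significant overall test.

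**Step 4: the rank branch.** No arithmetic is needed. Three conditions per person call for Friedman as the overall rank test, with paired signed-rank tests as follow-up. The breakfast sentence names only Wilcoxon and does not say which form.

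**The case against.** The strongest defence is that the breakfast sentence is shorthand. Repeated measures ANOVA and Friedman are named immediately before it, the power calculation is described as a repeated measures one, and the design is plainly a crossover. Wilcoxon may mean paired signed-rank tests after Friedman, which is a standard sequence. A journal article also condenses, so model terms may be in the full plan.

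Much of this stands. A reader might infer that the trial will be analysed as three independent groups, or that it has no valid rank test at all. The text establishes neither: it is ambiguous, and Friedman does appear in the section. The match to an unpaired sample size is consistent with the literal reading but does not prove it. What the defence does not remove is that the two adjacent sentences name different tests. If both concern breakfast, they conflict on the rank test. If only the second does, its wording does not fit the design.

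A reader might also infer a power of 58% by applying SD 10 to raw postprandial AIx, or a flat 1.83-fold inflation by using 0.7 as the between-visit correlation. Neither follows. The outcome is change in AIx, and 0.7 belongs to initial versus final measurements. On the stated outcome even the literal test keeps about the planned 80%.

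**Conclusion.** The concern holds as a fault of specification in the primary comparison, at the level of should-fix. If the sentence is followed literally, the cost is precision. Standard errors are 1.00 to 1.83 times what they need to be for r from 0 to 0.7, and the overall type I error is about 0.015 at r = 0.3 and 0.003 to 0.004 at r = 0.5, instead of 0.05. At r = 0 there is no loss.

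A reader might infer false positives; the error runs the other way. The sizes rest on SD of change 7.75, 38 completers, equal correlations between breakfasts and, above all, a value of r that the protocol does not supply. That Wilcoxon cannot be the overall test among three breakfasts does not depend on any of these.

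**What to change.** Replace the two test sentences with one prespecified within-subject analysis of AIx change. A suitable form is a linear mixed model in SPSS with participant as a random effect, breakfast, period and sequence as fixed effects, and baseline AIx as a covariate. Report the breakfast contrasts with 95% confidence intervals. State that this is the primary analysis whatever the Kolmogorov-Smirnov result, and check the model residuals instead.

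Keep Friedman, followed by paired Wilcoxon signed-rank tests, as a sensitivity analysis. A repeated measures ANOVA with breakfast explicitly named as the within-subject factor would also resolve the ambiguity about the error term; the mixed model has the advantage of taking period and sequence in directly.

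The cost is analysis wording only. The software is already named, and no new data or participants are needed.

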### Study procedures

On arrival at the research unit, subjects will be weighed, and their height, waist circumference and hip circumference will be measured. Participants will be seated and remain in this position throughout the visit. After 5 minutes of rest, a peripheral blood pressure measurement will be performed, and immediately the central blood pressure and haemodynamic parameters will be obtained. Next, cognitive performance will be assessed, fasting blood samples will be collected and central blood pressure and haemodynamic parameters will be determined again. Subjects will be provided with a randomly assigned breakfast to be consumed within 10 minutes. At the first bite, a timer will be started and additional measurements of central blood pressure and haemodynamic parameters will be taken every 15 minutes. Furthermore, another two cognitive performance evaluations and postprandial blood sampling will be completed at 60 and 120 minutes. Figure 2 shows the Standard Protocol Items: Recommendations for Interventional Trials (SPIRIT) diagram for the trial procedure.

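### The breakfast comparisons name no visit (period) term although each cognitive test is sat nine times over three visits; the cost is lost precision in the cognitive contrasts, not expected bias

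*Protocol article*

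**What the plan says.** Under Design and setting, "each subject will complete three interventions (control condition, high GI breakfast and low GI breakfast"), "with a washout period of one week between each trial". On allocation: "The order will be determined by a randomisation sequence generated using randomization.com software". The article does not say whether the orders are balanced.

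Study procedures places one cognitive evaluation before breakfast ("Next, cognitive performance will be assessed, fasting blood samples will be collected") and two after it: "another two cognitive performance evaluations and postprandial blood sampling will be completed at 60 and 120 minutes".

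Cognitive performance evaluation variables provides, for each evaluation, "a list of 15 different words from the Rey Auditory Verbal Learning Test and its alternative versions", and different letters for the fluency task. For the other tests no alternate form is stated, for example "The Trail Making Test A will be used to assess attention and processing speed". The same holds for Trail Making B, Digit Span Backward and Stroop.

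Statistical analysis names repeated-measures ANOVA or Friedman, then ANOVA or Wilcoxon across the three breakfasts with LSD post hoc tests. To control confounders, "a multivariate analysis will be performed using the general linear model (GLM) in basic or extended models". The model terms are not listed. Last menstruation date is the one modifier named, and it is given as an example.

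**The concern.** People tend to improve on timed and span tests when they repeat them. In a crossover that improvement follows visit number, which is known for every observation and can be modelled. If it is not modelled, it stays in the error term of the breakfast comparison.

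This matters here because cognition is part of the main aim (Objectives). The Discussion predicts that the high GI breakfast will favour attention, processing speed and working memory. The article measures these domains with Trail Making A, Stroop and Digit Span Backward, all among the tests with no stated alternate form. (Trail Making B is assigned to executive function.) So one of the two directional cognitive predictions rests on the outcomes most open to practice.

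**Working it through.** **The plan's own figure.** Sample size gives SD 10, correlation 0.7, a difference of 5 AIx points, alpha 0.05 (two-sided assumed) and power 0.80.
- SD of change = 10 × √(2 × (1 − 0.7)) = 7.75, so its variance is 60.
- n = 2 × (1.96 + 0.8416)² × 60 / 5² = 37.7, rounded up to 38.
- 38 / 0.95 = 40.

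The stated 40 reproduces. It concerns AIx, and nothing below changes it.

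**Number of sittings.** 3 evaluations × 3 visits = 9, over at least 2 × 7 = 14 days.

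**Variance of a breakfast contrast without a visit term (raw scores).** Let σ be the within-person SD and let practice add gσ per visit, linearly. The documents give no value for g, so it is an assumption shown over a range.
- Over the six possible orders, two breakfasts are one visit apart with probability 4/6 and two apart with probability 2/6. The mean squared gap is (4/6) × 1 + (2/6) × 4 = 2.
- Variance of one person's difference = 2σ² + 2g²σ² = 2σ²(1 + g²).

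Take a contrast that would have 80% power with 38 people if there were no practice. This is a yardstick only; the plan states no power for cognition. Power = Φ(2.8016/√(1 + g²) − 1.96), and the n that restores 80% is 37.67 × (1 + g²), rounded up.

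| g | variance × | power at n = 38 | n for 80% |
|---|---|---|---|
| 0.10 | 1.01 | 79.6% | 39 |
| 0.25 | 1.06 | 77.6% | 41 |
| 0.50 | 1.25 | 70.7% | 48 |
| 0.75 | 1.56 | 61.1% | 59 |
| 1.00 | 2.00 | 50.8% | 76 |

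**Simulation (3,000 runs per setting, n = 38).** With a 2-df visit term, power was about 78–80% at every g. Without it:
- *Orders in balanced blocks of six:* practice nearly cancels from the estimate but still inflates the residual. The test becomes conservative, with type I error 2.7% at g = 0.5 and 0.6% at g = 1.
- *Unrestricted orders:* type I error stayed near 5%, and practice moves the estimate by chance.

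**Size of the chance shift at n = 40.** Under unrestricted orders, the difference in mean visit number between two breakfasts has SD √(2/40) = 0.22. At g = 0.5 the shift has SD 0.5 × 0.224 = 0.112σ. Its square, 0.0125, equals the extra variance 2g²/40 = 0.5/40. The shift and the added variance are therefore one quantity and must not be added together. In balanced blocks the largest gap was 0.075 visits, or 0.5 × 0.075 = 0.0375σ.

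**Change from fasting.** A shift common to a whole visit cancels from the change score. A difference between visits in the gain made within the visit does not. On an illustrative logarithmic learning curve over nine sittings, the gain from fasting to 120 minutes is ln 3 − ln 1 = 1.10, ln 6 − ln 4 = 0.41 and ln 9 − ln 7 = 0.25 at visits 1, 2 and 3. This shows that some practice remains; it does not measure how much.

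**The case against.** The strongest reply is that an article condenses the full plan. The GLM is open-ended, its one named modifier is only an example, and visit could be among its unlisted terms. That is possible. But the tests named for the breakfast comparison itself carry no visit term, the rank alternatives have no place for one, and the GLM is justified by confounding rather than by the crossover structure. Following the text as written leaves visit in the error.

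Other parts of the reply stand:
- The practice gain is assumed, and the table treats it as linear across visits when it may flatten.
- The table is for raw scores. A fasting test is available at every visit, and the table does not apply to change from it.
- Changing word lists and letters reduces item learning for verbal memory and fluency. For the other tests the article is silent, which does not show that no alternate forms exist.
- The water condition carries the same kind of within-visit practice, and the plan already compares breakfasts with each other.

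A reader might infer more: that the contrasts are biased, that false positives are inflated, or that 40 not being a multiple of six spoils the design. None of these is supported. Random order removes bias in expectation, type I error is near nominal or below it, and the unequal numbers per order are nearly immaterial if orders are blocked.

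**Conclusion.** The point holds as a loss of precision in the cognitive contrasts. For raw scores the variance is multiplied by 1 + g². That is slight at g = 0.25 (1.06), material at g = 0.5 (1.25, power about 71% instead of 80%) and negligible below 0.25. These figures rest on an assumed linear gain per visit and on a yardstick contrast with 80% power. The effect on change-from-fasting scores is real in principle but unquantified.

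It would be tempting to extend this to the primary outcome. The documents do not support that: practice is not expected in AIx, and the sample size of 40 is unaffected. The change is worth making because it is cheap and protects a stated main aim, not because the trial's primary result is in doubt.

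**What to change.** Specify a linear mixed model or GLM for each breakfast comparison, above all for the cognitive outcomes, with subject, breakfast and visit number (1, 2, 3, as a categorical term). For cognition, base inference on between-breakfast contrasts at 60 and 120 minutes, adjusted for the same visit's fasting score, rather than on change within a breakfast.

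A sequence term is not needed: sequence is constant within a person, so with complete data it cannot alter these within-person contrasts.

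The cost is about 2 degrees of freedom and a revised analysis paragraph. Visit number is already known, so no new data are required.
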